### Data collection procedures

The recruitment was started on May 4, 2023, and the data collection is expected to complete in October 2023. Participants will have opportunities to select a time and location which is suitable for them. Meanwhile, a quiet and private interview room will be offered. Focus group discussions will be carried out in a booked conference room. The interviews and discussions will be facilitated by the first author, a female Chinese registered nurse (RN) and PhD candidate who had conducted qualitative studies and has received qualitative interviewing training from supervisors before data collection. The interview guides (Table 1) for interviews and focus group discussions are developed by the research team based on literature related to end-of-life communication [2, 3, 5, 6, 37–42]. The interview questions are designed in line with the research objectives and intended to invite various stakeholders to share end-of-life communication experiences, perceptions, strategies and suggestions in an open and supportive manner. The researcher will follow the interview and discussion process using prompts, including four main sub-topics of end-of-life communication, i.e., diagnosis and prognosis; advance care planning; goals of care; and death and dying [2, 3, 5, 6, 38], to ensure meaningful interviews and discussions. One or two patient-, family caregiver- pilot interviews and one pilot focus group discussion will be performed to troubleshoot issues with the interview process and questions and revise the interview guides if necessary [26, 43]. Pilot interviews will also aid in skilful and effective questioning in the formal study [44]. Sociodemographic data about participants will be collected via a brief self-developed questionnaire (S1 Appendix) at the end of each interview or focus group discussion. Each interview and focus group discussion will be expected to last 30–60 and 60–90 minutes, respectively. The interviews and discussions will be audio-recorded and transcribed verbatim in Mandarin first during data collection.

**Table 1 pone.0296342.t001:** Interview guides.

Patients and families	
Questions	Prompts
Experience	
Tell me about any communication experiences that you have had with healthcare providers.	What topics were covered?How did you communicate…? • Diagnosis and prognosis *(e*.*g*., *health condition; clinical course; treatment uncertainties and limitations; and life expectancy)* • Advance care planning *(i*.*e*., *discussions of future care; may include the individual’s concerns*, *wishes*, *values*, *understandings*, *and preferences)* • Goals of care *(i*.*e*., *discussions of current care and decisions; may include specific medical interventions*, *such as whether to utilise life-sustaining treatments)* • Death and dying *(e*.*g*., *end-of-life wishes; care for psychological*, *spiritual*, *and existential problems; arrangements after patients’ death; and bereavement support)* Who was present?When and where did the communication occur?
How did you feel about the communication?	Is anything impressive or annoying during the communication process? Why?
What do you think of the communication?	Are they good? Why?
Perception, attitude and belief	
If your (the patient’s) condition continues getting worse, or the curative treatment effect is not satisfactory, do you think it is necessary for healthcare providers to have end-of-life communication with you?	Why or why not?
What is your understanding of end-of-life communication?	Is anything important for you to discuss with healthcare providers?
Strategy	
How would you like the healthcare provider to have end-of-life communication with you?	How to communicate…? • Diagnosis and prognosis • Advance care planning • Goals of care • Death and dying What specific words or phrases do you think healthcare providers should use? Would you like to give me an example? Who do you think should initiate end-of-life communication with you? Who should be involved? When and where are appropriate?
Suggestion	
If you are invited to give suggestions to healthcare providers who would like to have end-of-life communication with you, what would you say?	E.g., for healthcare providers who do not have much experience in end-of-life communication

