Our previous review of the international literature on end-of-life communication strategies emphasised the imbalance between the amount of evidence from Anglo-Saxon and non-Anglo-Saxon nations, which hinders a thorough comprehension and comparison of end-of-life communication in various sociocultural situations [21]. Moreover, recent research findings reinforce the influence of Chinese culture and philosophy on end-of-life communication. For instance, the traditional understandings and conceptualisations of death (e.g., discussion about dying and death is taboo and regarded as unlucky and harmful) impede the promotion of end-of-life communication; and the family-centred decision-making style may conflict with patient’s autonomy [15]. Previous studies explored the working experiences of Chinese physicians and nurses who work with advanced cancer patients [22, 23]; nurses’ attitudes towards death and dying [24] and end-of-life care [25]; family communication experiences [26]; patients’ understanding of death [27] and advance directive preferences [28]. Nevertheless, little is known about Chinese patients, families and healthcare providers’ experiences and perceptions of client-provider end-of-life communication. In addition, no empirical evidence on end-of-life communication strategies from a Chinese perspective has been found.

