**Healthcare providers**	
Questions	Prompts
Perception, attitude and belief	
What is your understanding of end-of-life communication?	What topics include? E.g., disclosure of diagnosis and prognosis; advance care planning; goals of care discussions; talking about death and dying, etc.
What do you think about end-of-life communication between healthcare providers and patients and their families in hospitals?	If the patient’s condition continues getting worse, or the curative treatment effect is not satisfactory, do you think it is necessary for healthcare providers to have end-of-life communication with patients and their families? Why or why not?
Experience	
Tell me about any end-of-life communication experiences in your usual work.	What topics were covered? How did you communicate…? • Diagnosis and prognosis • Advance care planning • Goals of care • Death and dying Who was present? When and where did the communication occur?
How did you feel about the communication?	Is anything impressive or difficult during the communication process? Why?
How do you think your previous end-of-life communication?	Are they good? Why?
Strategy	
What, if any, specific strategies do you have that may be helpful for improving end-of-life communication between healthcare providers and patients and their families?	How to communicate…? • Diagnosis and prognosis • Advance care planning • Goals of care • Death and dying What specific words or phrases do you tend to use? Why? Would you like to give me an example? Who do you think should initiate end-of-life communication? Who should be involved? When and where are appropriate?
Suggestion	
What, if any, suggestions do you have for improving end-of-life communication between healthcare providers and patients and their families?	Are any other end-of-life issues that should be discussed? Any ideas about multi-professional end-of-life communication?
If you have the opportunity to participate in end-of-life communication skills training, what suggestions and expectations do you have?	What do you want to learn? What methods do you prefer?

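### The patient and family Strategy question takes for granted that end-of-life communication is wanted, although an earlier question allows the answer 'no'

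*Protocol article*

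**What the plan says.** Table 1 of the protocol article (Data collection procedures) prints one guide for patients and families and another for healthcare providers.

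In the patient and family guide, the block on perception, attitude and belief supposes that the illness worsens or that curative treatment disappoints. It then asks "do you think it is necessary for healthcare providers to have end-of-life communication with you", with a prompt for reasons in either direction. A question on what the person understands by end-of-life communication follows.

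The Strategy block then asks "How would you like the healthcare provider to have end-of-life communication with you". Its prompts cover the four sub-topics (death and dying is one), preferred words, who should be involved, when and where, and "Who do you think should initiate end-of-life communication with you". The Suggestion block asks "If you are invited to give suggestions to healthcare providers who would like to have end-of-life communication with you, what would you say".

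The provider guide words its Strategy question differently: "What, if any, specific strategies do you have that may be helpful for improving end-of-life communication". Its first Suggestion question has the same 'if any' form.

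On conduct, the text says: "The researcher will follow the interview and discussion process using prompts, including four main sub-topics of end-of-life communication". It states no exception for anyone who has called the communication unnecessary. The Introduction reports that, in the traditional Chinese view, "discussion about dying and death is taboo and regarded as unlucky and harmful".

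**The concern.** A question that begins with how a person would like something done assumes that the person wants it done. Here it is put to people who may have said, shortly before, that it is not needed. The guide offers them no neutral wording and no alternative question, so the easiest way to cooperate is to describe a form of communication they may not want.

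The Strategy answers are the direct patient and family input to objective 4, the development of culturally appropriate strategies. According to the Discussion, the study also informs the content of a training programme in the parent project. If reluctant or conditional answers are read alongside wanted ones, the material may look more accepting than the participants are. A preference for little or no such conversation would itself be an important cultural finding, and it could be under-reported.

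There is also a matter of care: the guide as written lets the death-and-dying prompt be used with a terminally ill person, or a relative, who has just indicated that the conversation is unnecessary.

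**Working it through.** No arithmetic bears on this point. The check is a reading of Table 1 in order, set against the rest of the article.

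1. **Is 'no' an allowed answer?** Yes. The necessity question can be answered yes or no, and its prompt asks for reasons for either.
2. **Is 'no' foreseeable?** Yes. The Introduction describes discussion of death as taboo, unlucky and harmful in the traditional view.
3. **Does the Strategy question allow for it?** No. It asks how, not whether. The prompt on who should initiate makes the same assumption. Nothing in the block is conditional on the earlier answer.
4. **Does the Suggestion question share the fault?** Only slightly. It is conditional, and it gives the wish to communicate to the provider. Advice not to raise the subject answers it fully. So, of the two later blocks, one is clearly affected and one marginally.
5. **Do other prompts capture a preference for less?** In part. The prompts on who initiates, who is involved, when and where can draw out waiting to be asked, or going through the family. None asks what should happen instead if the person wants no such conversation.
6. **Which death-and-dying prompt is at issue?** The detailed list (wishes, arrangements after death, bereavement) belongs to the Experience block, before the necessity question. Under Strategy only the bare sub-topic label appears.
7. **Does the analysis repair it?** Not by itself. Data analysis describes inductive coding by two independent researchers with constant comparison. The assumption enters when the question is asked, before any coding. No step is described that links a person's necessity answer to that person's strategy statements.
8. **Does it fit the study's own standards?** Poorly. Data collection procedures describes an open and supportive style, and Quality and rigor commits the researchers to setting assumptions aside.

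**Reach.** The guide is meant for about 20 patients and 20 family caregivers, so about 20 + 20 = 40 people would be asked the question. The documents contain nothing from which to estimate how many would answer 'no' or 'unsure'.

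**The case against.** The case on the other side is substantial.

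- **Necessity is not willingness.** The earlier question is hypothetical, and the construct is broad: diagnosis and prognosis, advance care planning, goals of care, death and dying. Someone who thinks the communication unnecessary, or who rejects only talk of death, may still have views on how a diagnosis should be discussed. This stands, and it is a reason to keep asking. It does not justify leaving out 'if at all'.
- **The provider guide is not a like-for-like comparison.** "What, if any, specific strategies do you have" asks whether providers have techniques, not whether the communication should take place. The provider guide has no branch after its own necessity prompt either. This also stands. The comparison shows only that open wording was available to the authors.
- **Participants are protected.** The interviews are semi-structured, questions may be refused, withdrawal is possible at any time, and Table 2 provides for pausing, stopping and support. These limit the harm. They rely, however, on the participant objecting or showing distress. The statement in Data management that interviews mainly recall past experience does not fit a question about what the person would want in future.
- **Pilots may lead to changes, and the interviews are held in Mandarin.** Both are true. No pilot criterion addresses this point. The English table is the only wording available to check; if the spoken Mandarin is already neutral, only the printed table needs correcting.

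A reader might infer that refusals are turned into strategies. The documents do not support this: the refusal and its reasons are recorded at the necessity question, a decliner can repeat them later, and no analysis rule recodes them. A reader might also infer that decliners are pressed to talk about death. The right to refuse and the distress protocol rule out that description. What can be said is that the written guide does not exempt them from the prompt.

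**Conclusion.** The point holds as a fault in the wording of one question. The patient and family Strategy question presupposes that end-of-life communication is wanted, and the guide has no neutral form and no follow-up for those who say it is unnecessary. The likely effect is a lean towards acceptance in the material for objective 4. Its direction is plausible from the wording, but its size cannot be stated, because the documents give no rate of 'no' answers. Any headcount of affected participants would be a guess and should not be used.

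The conclusion rests on two assumptions: that the printed English reflects what is asked in Mandarin, and that interviewers broadly follow the guide. It does not claim that both later questions are faulty, or that the safeguards are absent. It is a worthwhile, nearly costless improvement and does not put the study's design in doubt.

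**What to change.** - Reword the Strategy question to begin 'How, if at all, would you like ...'.
- After a 'no' or 'unsure' answer on necessity, add one probe: 'What would you prefer providers to do instead?'
- For those participants, check willingness before using the four sub-topic prompts under Strategy.
- In the analysis, link each participant's necessity answer to that person's strategy statements, so that a preference for no or limited communication is reported as a finding and is not merged with wanted strategies.

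The Suggestion question can stay as it is. For interviews already completed, only the last step can be applied, and it needs only the transcripts.

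The cost is one wording change, one probe, one check by the interviewer and one link in the coding. The downside is somewhat fewer strategy statements from people who decline. The probe should recover part of that loss as information on what they would prefer.

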**Healthcare providers**	
Questions	Prompts
Perception, attitude and belief	
What is your understanding of end-of-life communication?	What topics include? E.g., disclosure of diagnosis and prognosis; advance care planning; goals of care discussions; talking about death and dying, etc.
What do you think about end-of-life communication between healthcare providers and patients and their families in hospitals?	If the patient’s condition continues getting worse, or the curative treatment effect is not satisfactory, do you think it is necessary for healthcare providers to have end-of-life communication with patients and their families? Why or why not?
Experience	
Tell me about any end-of-life communication experiences in your usual work.	What topics were covered? How did you communicate…? • Diagnosis and prognosis • Advance care planning • Goals of care • Death and dying Who was present? When and where did the communication occur?
How did you feel about the communication?	Is anything impressive or difficult during the communication process? Why?
How do you think your previous end-of-life communication?	Are they good? Why?
Strategy	
What, if any, specific strategies do you have that may be helpful for improving end-of-life communication between healthcare providers and patients and their families?	How to communicate…? • Diagnosis and prognosis • Advance care planning • Goals of care • Death and dying What specific words or phrases do you tend to use? Why? Would you like to give me an example? Who do you think should initiate end-of-life communication? Who should be involved? When and where are appropriate?
Suggestion	
What, if any, suggestions do you have for improving end-of-life communication between healthcare providers and patients and their families?	Are any other end-of-life issues that should be discussed? Any ideas about multi-professional end-of-life communication?
If you have the opportunity to participate in end-of-life communication skills training, what suggestions and expectations do you have?	What do you want to learn? What methods do you prefer?

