### Data analysis

The data collection and analysis will be conducted simultaneously. Transcripts of interviews and focus group discussions will be entered into NVivo (QRS International, Victoria, Australia). The data analysis will be an iterative, cyclic and self-reflective process. Using inductive thematic analysis, common themes and categories will be determined through inductive reasoning and constant comparison, meaning there is no theoretical perspective to guide coding or explanation [45]. Two researchers will work independently following six interactive steps of thematic analysis: getting familiar with collected data, generating initial codes, searching for appropriate themes, reviewing these themes, defining themes, and presenting and discussing findings [45]. Any discrepancies will be discussed in a regular meeting with all research team members. A consensus will be established after discussions on potential codification differences. Participants will be given the transcriptions and analysis results for verification. The data analysis will be performed in Chinese. Two researchers fluent in Chinese and English and have experience translating qualitative research reports will translate significant statements, categories, and themes into English for reporting. To enhance accuracy, the translation results will be examined by the third researcher who is also bilingual in English and Chinese. Any disagreements in translation will be resolved through discussion. The Standards for Reporting Qualitative Research (SRQR) checklist (S2 Appendix) will be followed [46].

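### The provider guide's opening question lists the study's own four sub-topics as examples, so it cues the concept it should elicit, and prompted content is not separated from spontaneous content

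*Protocol article*

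**What the plan says.** The Data collection procedures section says the guides "are developed by the research team based on literature related to end-of-life communication", and that the researcher will conduct sessions "using prompts, including four main sub-topics of end-of-life communication, i.e., diagnosis and prognosis; advance care planning; goals of care; and death and dying". The four sub-topics are cited to literature.

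Table 1 sets questions and prompts in separate columns.

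- **Provider guide.** The first question asks for the participant's understanding of end-of-life communication. Its prompt is "What topics include? E.g., disclosure of diagnosis and prognosis; advance care planning; goals of care discussions; talking about death and dying, etc". The same four topics return as prompts under Experience and under Strategy.
- **Patient and family guide.** The first question, under Experience, asks about any communication with healthcare providers; its prompts list and explain the four topics. The understanding question comes later, and its prompt is open: "Is anything important for you to discuss with healthcare providers". The four topics return under Strategy.

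The Data analysis section declares a thematic analysis of the inductive kind and explains the term as "meaning there is no theoretical perspective to guide coding or explanation". Objective 2 is to understand participants' perceptions, attitudes and beliefs. Objective 4 is to develop communication strategies suited to Chinese culture.

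**The concern.** Objective 2 depends on how participants themselves conceive of end-of-life communication. The provider question that bears on this most directly comes with the researchers' answer attached. In a focus group, every member hears the cue at once.

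If the four topics then appear as themes, a reader cannot tell whether providers raised them or the guide did. If providers would have drawn the boundary elsewhere, for example by including matters outside the four topics, that content may be under-elicited. Objective 4 is exposed for the same reason: strategies meant to reflect the Chinese setting should rest on content whose origin, volunteered or suggested, is known. The Discussion intends these data to inform a training programme, so the uncertainty would carry forward.

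**Working it through.** No statistical figure is involved. The check compares the text of the sections and counts the guide questions.

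**1. Is the provider prompt the study's own concept?** The Introduction's definition and the provider prompt line up almost item by item.

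| Introduction's definition | Provider prompt, question 1 |
|---|---|
| Prognosis disclosure | Diagnosis and prognosis disclosure |
| Advance care planning | Advance care planning |
| Goals of care | Goals of care |
| Death and dying (the overall subject) | Death and dying |

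The only addition is diagnosis. The prompt supplies the researchers' definition.

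**2. How often does the four-topic list accompany a question?** Counted by hand from Table 1.

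| Guide | Questions | With the list | Where |
|---|---|---|---|
| Patients and families | 3 + 2 + 1 + 1 = 7 | 2 | First Experience question; Strategy |
| Providers | 2 + 3 + 1 + 2 = 8 | 3 | Understanding; first Experience question; Strategy |
| Both | 15 | 5 | |

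So 15 − 5 = 10 questions carry no list. By section, the list appears in 2 of 4 for patients and families and 3 of 4 for providers.

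**3. Where does the understanding question stand?** For providers it is question 1 of 8, with the list attached. For patients and families it is question 5 of 7, without the list, but after question 1 has introduced the topics. The cue is direct in one guide and indirect in the other.

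**4. How many sessions does the direct cue reach?** The Participants section plans 3 to 6 focus groups of 4 to 8 people, that is 3 × 4 = 12 to 6 × 8 = 48 providers, plus any provider interviewed individually. The indirect cue concerns about 20 + 20 = 40 patient and family interviews. Both figures assume that the interviewer uses the prompts as printed.

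**5. Does another provision neutralise the cue?**

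- The Data collection procedures section plans the sub-topics as prompts but does not say that they follow an open answer.
- Bracketing and reflexive notes (Quality and rigor) address the researchers' preconceptions, not words that participants hear.
- Member checking tests whether an account is accurate, not whether it was volunteered.
- Independent coding by two researchers cannot recover content that was not elicited.
- The provider prompt about further end-of-life issues comes under Suggestion, after the list has been used three times.
- The pilot step allows the guides to be revised, but does not target this point.

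None of these separates prompted from unprompted content.

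**The case against.** The strongest reply is that this is ordinary semi-structured interviewing. The question itself is open; the list sits in a separate prompt column, follows an open sub-question and is hedged as examples. An experienced interviewer would probably use it only when an answer runs dry. Two thirds of the questions carry no list. In a setting where the Introduction describes death as a taboo subject, prompts are a defensible way to reach what people will not volunteer.

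Much of this stands. It limits the size of the point and argues against discarding prompted content. It does not answer why the definitional question needs the list when the same topics are probed under Experience and Strategy, and the sequence it assumes is not written down.

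A reader might infer more than the documents support:

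- *That the plan contradicts itself.* The inductive statement is confined to coding and explanation. A topic guide for data collection is compatible with inductive coding, and no prior codebook is described.
- *That both guides attach the list to the understanding question.* Only the provider guide does.
- *That the four topics are an Anglo-Saxon import.* The Introduction reports "the imbalance between the amount of evidence from Anglo-Saxon and non-Anglo-Saxon nations", but in the team's review of communication strategies. That review is not among the references given for the sub-topics, and the cultural origin of those references is not shown.
- *That the two guides should run in the same order.* Opening with general communication experience is a gentler start for terminally ill patients and their families. The sensitivity of the subject, stressed under Data management and in the Discussion, is a reason to keep it. Comparing patients with providers is also not a stated objective.

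**Conclusion.** The point holds in a narrow form. One provider question, the one most directly aimed at objective 2, carries a leading example list. The protocol neither makes the sub-topic prompts conditional on a spontaneous answer nor separates the two kinds of content in coding. For patients and families the priming is indirect and weaker.

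The size is 5 of 15 questions with the list, and one guide of two with it at the understanding question. The consequence is a risk to the interpretation of objectives 2 and 4; the documents do not show that the themes will reproduce the prompts. The conclusion assumes that prompts are used broadly as printed. If interviewers already hold them back until the open answer is complete, the risk is smaller, but the protocol should then say so. The change is worth making because it reduces a plausible bias at almost no cost.

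**What to change.** 1. Delete the example list from the provider understanding question. The topics remain covered under Experience and Strategy.
2. State in both guides that the four sub-topics are follow-up probes, used only after the participant has answered the open question.
3. Add one attribute in NVivo that tags each segment as spontaneous or prompted. Report both kinds and discard neither.
4. Flag sessions run with the present wording. Recruitment began on May 4, 2023, so there may be some, or all may be complete. The verbatim transcripts still allow the tagging in step 3.
5. Keep the experience-first order for patients and families, and keep the description of the analysis as inductive.

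The cost is minor editing of the guides, which the pilot step already allows for, and one extra coding attribute. Sessions held before and after the edit will differ slightly in wording, which the flag makes visible.
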